### Primary Outcomes Measure

#### WHOQOL-BREF

Developed by the World Health Organization, the instrument is a short version of WHOQOL-100, and it comprises 26 items in which two are general about quality of life and general health, and the other 24 grouped into four domains: physical health, psychological health, social relationships, and environment. It presents Likert scale answer (1–5 points). The Brazilian validation of WHOQOL-BREF Cronbach coefficient values has satisfactory internal consistency ranging from 0.69 to 0.84 between the domains (61).

The WHOQOL-OLD module will be used as a complement to the WHOQOL-BREF to evaluate the quality of life of the elderly. The WHOQOL-OLD follows the same methodology as WHOQOL-100, but the objective is evaluating the specific quality of life of the elderly population. The module comprises 24 items evaluated by the Likert scale (1–5 points) assigned six facets such as sensory abilities, autonomy, past–present–future activities, social participation, death and dying, and intimacy. The Brazilian validation of WHOQOL-OLD also has a satisfactory internal consistency with its Cronbach coefficient between 0.71 and 0.88 (60).

### Secondary Outcomes Measures

#### MAAS

It is a unidimensional 15-item scale that assesses the level of mindfulness or consciousness in the present moment of the individual (66). It was validated in Brazil by Barros et al. (65), and it has a satisfactory internal consistency and reliability with the Cronbach coefficient of 0.83.

#### SCS

It was developed by Neff (67) to measure the level of self-compassion of the individual. The SCS consists of 26 items divided into six subscales for self-kindness, self-judgment, mindfulness, common humanity, and isolation. The answers are given in 5 points of the Likert scale, which (1) is almost never and (5) is almost always. The Brazilian validation was made by Souza and Hutz (78), and it has good internal consistency with Cronbach α of 0.92 for the 26 items.

#### DASS-21

In order to assess psychological health, we will use the DASS-21. It is a 21-item scale that measure and divide the symptoms of anxiety, depression, and stress, in which participants indicate the degree to which they experienced these symptoms in the previous week on 7 items in each subscale. It is a Likert scale of 4 points between 0 and 3. The highest score in each subscale refers to more negative affective states (69). It was adapted into the Brazilian Portuguese language by Vignola and Tucci (70) presenting Cronbach α of 0.92 for the subscale of depression, 0.90 for the stress, and 0.86 for anxiety. Gloster et al. (79) suggest that DASS-21 is an effective instrument when applied in the elderly population.

#### PSQI

The PSQI is an instrument that evaluates the sleep quality of individuals in the last month. It comprises 19 questions in self-report and 5 questions answered by some third party in which it will be made by phone call to a caregiver, relative, or spouse (72). It was validated for Brazilian population (71), and it showed a good internal consistency with Cronbach α of 0.82. The components of the PSQI are subjective sleep quality, sleep latency, sleep duration, habitual sleep efficiency, sleep disturbance, use of sleeping medication, and daytime dysfunction. Categorized as seven components in scores from zero (no difficulty) to three (severe difficulty). The sum of the results can range from 0 to 21 scores, where the higher the number, the worse the quality of sleep. A total score of <5 indicates that the individual is experiencing difficulty in at least two components or moderate dysfunctions in at least three (80).

The Duke University Religion Index is a 5-item scale that measures three major dimensions of religiousness: (1) organizational, the frequency of attending public religious activities and group-related; (2) non-organizational, which involves religious activities performed in private, such as prayer, scripture study, watching religious TV, or listening to religious radio; (3) intrinsic religiosity, assessing the degree of personal religious commitment or motivations (74, 81), and it has adequate internal consistency in the Brazilian version (73).

#### MoCA

This neuropsychological test assesses the cognitive function. It is a 12-item test that measures eight cognitive domains: short-term memory (delayed drawing), visuospatial abilities (cube drawing, clock drawing), executive function (trail-making test, phonemic verbal fluency, verbal abstraction), attention, concentration, working memory, language, and orientation to time. The test total score is 30 points where a score ≤26 indicates normality, and less indicates mild cognitive impairment (63, 64).

At the post-intervention, the feasibility and adherence of MBHP program among the participants will be assessed through a questionnaire created by our research group in order to evaluate the type, frequency, and length of personal meditative practice at home during the week out of the meetings, addressing potential unwanted effects as well. The frequency of the attendance to the weekly meeting will also be monitored. The dropout cases will be monitored, and we will make phone calls to them to ask the reasons why they were absent or did not go on attending the meetings. For more information about the target of each scale assessment and its time points, see Table 2 and Figure 2 to see each step of the study.

**Table 2 T2:** Overview of measures and time points (according to 2013 SPIRIT figure guidelines).

**Measure**	**Target**	**T0**	**T1**	**T2**
		**Baseline**	**Post-intervention**	**Follow up**
WHOQOL-BREF	Quality of life	X	X	X
WHOQOL-OLD	Quality of life of elderly	X	X	X
MoCA	Cognitive function	X	X	X
CDR	Dementia	X		
ADL	Activities of daily living	X	X	X
MAAS	Mindfulness trait	X	X	X
SCS	Self-compassion	X	X	X
PSQI	Sleep quality	X	X	X
DUREL	Religiosity	X	X	X
DASS-21	Psychological health	X	X	X

*ADL, Activities of Daily Living Scale; CDR, Clinical Dementia Ratings; DASS-21, Depression Anxiety Stress Asessment-21; DUREL, Duke Religious Index; MAAS, Mindful Attention Awareness Assessment; MoCA, Montreal Cognitive Assessment; PSQI, Pittsburgh Sleep Quality Index; SCS, Self-Compassion Scale; WHOQOL-BREF, World Health Organization Quality of Life–BREF; WHOQOL-OLD, World Health Organization Quality of Life–OLD*.

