## Abstract

**Introduction:** Population aging is a global phenomenon that has grown rapidly and progressively all over the world. Interventions that promote health must be studied and implemented to make the aging process be with quality of life. Depression and anxiety are the most common mental health conditions that compromise the quality of life on the elderly and it can cause damage to the autonomy and activities of daily life. Mindfulness training has been shown to improve psychological health and quality of life on adults. Studies involving Mindfulness-Based Interventions (MBIs) with older people are scarce in the literature, but they have been increasing in recent years showing promising results for healthy aging. This trial will investigate the feasibility and preliminary efficacy of an MBI on the quality of life of elderly assisted in the Primary Care.

**Materials and Methods:** A cohort-nested randomized controlled trial with 3 assessment points (baseline, post-intervention and 1-year follow up) will be conducted to compare a MBI program (Mindfulness-Based Health Promotion) to a cognitive stimulation control-group in a Primary Care facility. One-hundred and two older adults will be recruited from a cohort of this facility and they will be randomized and allocated into an intervention group (*N* = 76) and the control group (*N* = 76). The primary outcome evaluated will be the improvement of quality of life assessed by the WHOQOL-BREF and WHOQOL-OLD. The secondary outcomes will be cognitive function, psychological health, sleep quality, self-compassion, and religiosity. Qualitative data will be assessed by focus group and the word free evocation technique. The feasibility of the program will also be evaluated by adherence and unwanted effects questionnaires.

**Discussion:** This cohort-nested clinical trial will be the first mixed-methods study with 3 assessment points which will study the feasibility and preliminary efficacy of a mindfulness-based program for older people in Latin America population. If the findings of this study confirm the effectiveness of this program in this population it will be possible to consider it as intervention that might be implemented as public policy addressed to older people in healthcare systems.

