## Materials and Methods

The “MBHP-Elderly Study” is a randomized controlled trial addressing older people with 3 assessment points (baseline, post-intervention, and 1-year follow-up) nested in a cohort study (the EPIDOSO study) of older adults patients assisted in a PC facility of the “Center for Aging Research” [Centro de Estudos do Envelhecimento (CEE)] of the Universidade Federal de São Paulo—UNIFESP.

One hundred fifty-two participants will be recruited from the cohort and then randomized into the following two experimental groups: (I) MBHP intervention group (76 participants) in which the elderly will have a weekly meeting of an hour and 30 min for 8 weeks to perform the MBI (MBHP protocol) accompanied by extra four 1-h meetings through a maintenance group with all participants after the eighth week (each maintenance session took place fortnightly), totaling a 4-month (16-week) intervention; (II) cognitive stimulation control group (76 participants) of elderly who will take computer-based cognitive stimulation classes for 4 months, once-a-week 1.5-h meetings without maintenance phase, totaling 16 weeks. In both groups, the same assessment for data collection will be applied, and they will be applied in the baseline (T0), post-intervention (T1), and 1-year follow-up (T2). Both interventions will last 16 weeks. However, the reason why the MBHP intervention group will take 12 sessions and the cognitive stimulation control group 15 sessions is because one of the aims in the MBHP intervention is to work on the participants' autonomy in their personal mindfulness practice in daily life through home activities exercises, and we wanted to compare its outcomes with the 4-month weekly meetings of control intervention, which require face-to-face sessions. Study design and participant flow through the trial is shown in Figure 1.

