The main techniques used in this program are “mindfulness in breathing,” “body scan,” “mindful walking,” “mindful movements,” and “3 min of mindfulness” (adapted from the program of the Breathworks Institute, UK). It also introduced the concepts of “first and second suffering” and the “Hi-Thanks-Bye” as psychoeducation techniques. The compassion and self-compassion practices are also included in the protocol, which might be useful for older people dealing with the self-criticism and low levels of acceptance of body changes. There is no consensus about potential unwanted effects of MBIs in the literature yet (55).

In this study, the MBHP sessions will be adapted and abbreviated for 1 h and a half per week for 8 weeks. After the 8-week protocol, four 1-h maintenance sessions will be performed every 15 days to match a 4-month intervention time period in full. We chose this format and length to be able to compare with the active control group (as described below). Moreover, studies that applied MBIs for longer months with older adults have been previously reported and may be beneficial to them (56, 57), as well as meeting lasting 1 h and 30 min instead of 2 h during the 8-week program (29, 30).

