### Recruitment, Procedures, and Randomization

Overall, 152 elderly were recruited from the cohort of the CSR of the Universidade Federal de São Paulo from June 2018 to May 2019. Recruitment was conducted by invitation phone calls to the cohort list. Participants who showed interest in the research were scheduled to visit the center so that one of five researcher assistants would apply a comprehensive geriatric and gerontological evaluation named as Wide Geriatric and Gerontologic Assessment (WGGA), which comprise sociodemographic data and other measures' information needed for the recruitment such as GDS-15 (49–51) and baseline data such as quality of life [World Health Organization Quality of Life (WHOQOL) BREF and WHOQOL-OLD] (59–62) and ADLs, and then the MoCA (63, 64) is applied in order to evaluate cognitive function.

After this first step, a trained gerontologist applies the CDR (47, 48, 52) to evaluate if the participant has dementia or any cognitive impairment. The CDR evaluation requires a caregiver or a relative close to the older adult to be interviewed to inform about his cognition and behaviors (48). The participants who score 0 or 0.5 were included in the study.

After the screening and recruitment, the 152 participants approved in the inclusion criteria will be randomized and allocated into the groups. Married participants who meet the inclusion criteria will be allocated to the same groups; it was decided to do that because some couples need the support from one another to go to the center. The MBHP program group will then be randomized again into other four subgroups (19 participants each) because the MBI group is better availed when smaller. All the groups will follow the same assessment of the research, and the MBHP protocol will be led by instructors certified by Mente Aberta the whole time. The control group will also be randomized and allocated into small groups according to the number of computers in the computer lab (19 participants each).

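### Unwanted effects are described only inside an MBHP home-practice questionnaire, with no control-arm counterpart, so read naturally they give a one-arm rate with no randomized comparator

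*Protocol article*

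**What the plan says.** The closing paragraph of the MoCA subsection, under Secondary Outcomes Measures, is the only description of how unwanted effects are collected. It says that "the feasibility and adherence of MBHP program among the participants will be assessed through a questionnaire created by our research group". The questionnaire covers the kind, frequency and duration of meditation practised at home "during the week out of the meetings, addressing potential unwanted effects as well". It is given once, after the intervention. Table 2 does not list it, and the Statistical Analysis section names no analysis of unwanted effects.

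The Abstract uses this information to judge feasibility: "The feasibility of the program will also be evaluated by adherence and unwanted effects questionnaires". The MBHP Protocol section gives a reason to look: "There is no consensus about potential unwanted effects of MBIs in the literature yet".

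Two statements point towards equal assessment of the arms. Materials and Methods says "In both groups, the same assessment for data collection will be applied", at T0, T1 and T2. Recruitment, Procedures, and Randomization says "All the groups will follow the same assessment of the research".

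**The concern.** The form is tied to one programme, and its other questions concern meditating at home. Those questions do not fit people attending a computer class, and nothing is described in their place for the control arm. On that reading, the randomized control group supplies no background rate for unwanted effects.

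This matters because feasibility is one of the trial's aims and unwanted effects are part of how it is to be judged. Participants are 60 or older. Some will report low mood, worry or poor sleep over 16 weeks whatever class they attend. A high MBHP count might be only that background, and a low count would not show that MBHP is as well tolerated as the control. The Discussion looks ahead to use in other facilities and in public policy, where a reader would want this comparison. The trial already has a concurrent control of equal duration that could provide it.

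**Working it through.** **Which arm is asked**

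| Place in the protocol article | What it settles |
|---|---|
| MoCA subsection, closing paragraph | Form concerns MBHP feasibility and home meditation, at T1 only; no control version described |
| Abstract | Feasibility of the programme; arm not named |
| Table 2 | Form not listed |
| Materials and Methods | Same assessment in both groups, referring to the battery repeated at T0, T1 and T2 |
| Recruitment, Procedures, and Randomization | All groups assessed alike; the sentence stands between the split of MBHP into subgroups and the split of the control group, so it may mean the MBHP subgroups |

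No sentence says that controls are asked about unwanted effects, and none says that they are not. A one-arm form is the natural reading, but it is an inference.

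**Sample size used below**

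The protocol gives no unwanted-effect rate to reproduce. Its 64 per arm follows from a two-sided t-test at α = 0.05 and power 0.80 with a standardized difference of 0.5 (63.8, rounded up). The 0.5 is an assumption, because no effect size is stated. Allowing for 15% loss, 64/0.85 = 75.3, so 76 per arm.

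**What one arm can show (64 MBHP completers)**

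- No events: the two-sided exact 95% upper limit is 1 − 0.025^(1/64) = 5.6%. The one-sided limit is 1 − 0.05^(1/64) = 4.6%.
- 13 of 64 (20.3%): exact 95% interval 11.3% to 32.2%.
- Neither result gives a difference. For an MBHP rate of 20%, unmeasured control rates of 10%, 20% and 30% would mean differences of +10, 0 and −10 points.

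**What two arms could show (assumed equal true rates)**

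95% half-width = 1.96 × √(2p(1 − p)/n).

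- p = 20%, n = 64: 1.96 × √(2 × 0.2 × 0.8/64) = 1.96 × 0.0707 = 13.9 points.
- p = 10%: 10.4 points with 64 per arm, 9.5 with 76.
- p = 5%: 7.6 points with 64 per arm, 6.9 with 76.

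**What planned data can show**

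Table 2 lists the DASS-21 at T0, T1 and T2, and its subsection gives the direction of harm: "The highest score in each subscale refers to more negative affective states". With the Cronbach α values quoted there, the reliable-change threshold in SD units is 1.96 × √2 × √(1 − α):

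- depression, α = 0.92: 0.78 SD
- stress, α = 0.90: 0.88 SD
- anxiety, α = 0.86: 1.04 SD

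**The case against.** The strongest reply is that this is a condensed article, and that a programme-specific feasibility form is a within-programme question for which no comparison between arms was promised. The superiority hypothesis concerns benefits, and policy use is made to depend on effectiveness. The same-assessment statement in Materials and Methods concerns the repeated battery, so a T1-only form need not conflict with it. Table 2 also omits attendance and dropout monitoring, so absence from it proves little. All of this stands, and it limits the point.

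Three stronger readings are therefore not supported:

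- A reader might infer that controls are definitely not asked. The article never says so.
- A reader might infer a contradiction with the same-assessment statements. One refers to the T0/T1/T2 battery and the other is ambiguous, so there is a tension and no more.
- A reader might infer that the control arm plays no part in assessing harm. The DASS-21, PSQI, MoCA and ADL are measured at all three time points, and changes between groups are to be compared. Average worsening is therefore already comparable by arm. Dropout calls are not restricted in words to MBHP.

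The reply leaves a gap. Average change is not a count of people who got worse, and reasons for dropping out are not an unwanted-effect rate. Focus groups draw only on people who attended at least 75% of sessions, so they will tend to miss those who left because of an unwanted effect. If controls do receive the form, its meditation questions do not suit them and the description needs rewording. If they do not, there is no comparison.

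**Conclusion.** The point holds in a limited form. As described, unwanted effects sit in an MBHP home-practice questionnaire with no stated control counterpart. Read naturally, this yields a one-arm rate that cannot be compared with, or attributed over, the active control, and the sign of the difference would be unknown. The primary outcome, the sample size and the planned efficacy comparisons are unaffected.

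Asking both arms would not give a sharp answer. The ±14 points assumes 20% in each arm and 64 completers per arm, and rates of 5% to 10% would give about ±7 to ±10 points. All these rates are illustrative, since the article gives none. Even so, an imprecise randomized comparison is more informative than a count with no comparator, and it costs little.

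**What to change.** 1. State which arm receives the unwanted-effects items. Separate them from the home-practice items, word them neutrally (for example, asking about the time since the classes began), ask them identically in both arms at T1, and tabulate by arm. Use the same mode of collection if possible: Assessment and Outcomes plans paper for MBHP and SurveyMonkey for controls, and mode alone could shift the answers.
2. This can apply only where T1 is still to come. The article puts recruitment between June 2018 and May 2019 and the end of follow-up collection in February 2021. Where T1 has passed, report the MBHP count as descriptive and say that it cannot be attributed to the programme.
3. In either case, report by arm the proportion with reliable worsening on each DASS-21 subscale from T0 to T1 and from T0 to T2, using 0.78, 0.88 and 1.04 SD for depression, stress and anxiety and the trial's own baseline SD. The α values come from a validation study, and this trial excludes people scoring 7 or more on the GDS-15, so present the thresholds as approximate. The paper/SurveyMonkey difference affects this table too and should be noted beside it.

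The cost is some protocol wording, one short form at a visit already held (a few minutes of each control participant's time) and one extra table. The DASS-21 table needs no new data.

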### Statistical Analysis

All analyses will be conducted using intention-to-treat and per-protocol analyses following the CONSORT recommendations for reporting the results (44).

Categorical variables will be described by absolute and relative frequencies. Numerical variables will be checked for their distributions through histograms and boxplots. If considered as having normal distribution, they will be described by mean and standard deviation. Otherwise, they will be described by medians and quartiles.

The primary outcome of this study is the quality of life measured by the WHOQOL-BREF and WHOQOL-OLD, and the secondary outcomes are cognitive function measured by the MoCA, level of consciousness at present measured by the MAAS, self-compassion measured by the SCS, Psychological Health measure by DASS-21, sleep quality measured by PSQI, and religiosity assessed by the Duke University Religion Index. Sociodemographic questions (sex, age, schooling), treatment group, and time will be the independent variables.

To verify the homogeneity between the study groups regarding sociodemographic measures at the initial time of the study, the groups will be compared by means of hypothesis tests of the type: χ^2^ and/or Fisher exact for categorical variables and multivariate analysis of variance (MANOVA) and/or Kruskal–Wallis for numerical or ordinal variables. A descriptive analysis of the sociodemographic categories regarding the sex, age, and schooling of both groups will be carried out.

Measures of preintervention (T0), post-intervention (T1), and follow-up (T2) outcomes may be compared by means of MANOVA for repeated measures. If necessary, Student *t*-tests will be conducted for paired or Wilcoxon data by applying corrections by the Holm or Bonferroni method. A Pearson correlation coefficient analysis will also be performed between the means of the primary outcomes and those of the secondary outcomes to examine the degree of changes in the outcome measures over time.

The difference between the measures T0 to T1, T1 to T2, and T0 to T2 can be compared between the intervention groups in MANOVA of repeated measures by means of Mann-Whitney tests. If necessary, these models will also be adjusted to assess the effects of time and intervention group, controlling for possible moderating variables.

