### Sample Size and Power Calculations

The minimum sample for each group was identified as 64 participants to detect a power of 0.80 and an α of 0.05. These calculations were performed using the G^*^Power 3.1 software for comparison between two intervention groups with respect to the mean differences of the scores at each time point of assessment relative to baseline. Therefore, 152 individuals should be randomized to receive one of the interventions (76 in the intervention group, 76 in the control group) assuming a maximum loss of 15%.

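### Quality of life is primary on two instruments, with no named lead score, time point, analysis set or win rule, and no binding multiplicity rule for the between-arm tests

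*Protocol article*

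**What the plan says.** All references are to the protocol article.

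- **Primary outcome (Statistical Analysis).** "The primary outcome of this study is the quality of life measured by the WHOQOL-BREF and WHOQOL-OLD". Neither instrument is ranked first, and no total or summary score is named for either.
- **Structure of the instruments (Primary Outcomes Measure).** WHOQOL-BREF has two general items, with "the other 24 grouped into four domains". WHOQOL-OLD has 24 items "assigned six facets such as sensory abilities" and five others. It is introduced as a complement to WHOQOL-BREF.
- **Analysis sets (Statistical Analysis).** "All analyses will be conducted using intention-to-treat and per-protocol analyses". Neither set is given precedence.
- **Tests (Statistical Analysis).** Repeated-measures MANOVA is offered as something that may be used. Holm or Bonferroni appears in the sentence on paired t or Wilcoxon tests, to be used if needed, with no family defined. A later paragraph compares changes between arms for T0 to T1, T1 to T2 and T0 to T2, and states no correction.
- **Sample size.** "The minimum sample for each group was identified as 64 participants to detect a power of 0.80 and an α of 0.05". The calculation is for a "comparison between two intervention groups with respect to the mean differences of the scores at each time point of assessment relative to baseline". No instrument, single time point, effect size or division of alpha is given.
- **Hypothesis (end of the Introduction).** The MBHP programme is expected to be superior to cognitive stimulation.

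**The concern.** A trial with a superiority hypothesis needs a rule, fixed in advance, for what counts as a positive result. Here two instruments, at least two post-baseline times and two analysis sets all carry the primary label, and the only multiplicity rule sits on within-arm tests that do not address superiority. The optional MANOVA is not made a gate that must be passed before individual contrasts are read.

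Two things are at stake. If any one favourable between-arm result may be called success, the error rate is not the 5% used to size the trial. If instead both instruments must succeed, the error rate is protected, but the power behind 64 per arm is not the power of that joint claim. The article does not choose, so neither its alpha nor its power attaches to a defined claim.

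**Working it through.** **Inputs.** From the article: alpha 0.05, power 0.80, 64 evaluable and 76 randomised per arm, 15% loss, 1:1 allocation, two primary instruments, post-baseline times T1 and T2. Assumed, because not stated: a two-sided test, a standardised difference d = 0.5, and the correlations given below.

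**1. The plan's own figure.** A two-sample t-test at two-sided 0.05 with 80% power and d = 0.5 needs 64 per arm, and power at 64 is 80.1%. Other effect sizes give 100 (d = 0.4), 79 (0.45), 53 (0.55) and 45 (0.6). One-sided at d = 0.5 gives 51. Loss: 64 / 0.85 = 75.3, so 76 per arm and 152 in total. The figure therefore matches a single test at the full 0.05, given d = 0.5.

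**2. False-positive rate if any one success counts.**

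- Two instruments, one time, independent: 1 − 0.95² = 9.8%. With correlation 0.3–0.7 between scores: 8.4–9.5%.
- Two instruments × two times, independent: 1 − 0.95⁴ = 18.5%.
- The same four tests, correlated: the probability that the largest of four |Z| exceeds 1.96, simulated from a multivariate normal.

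| Correlation between scores | Correlation between times | At least one false positive |
|---|---|---|
| 0.3 | 0.5 | 16.9% |
| 0.3 | 0.7 | 15.7% |
| 0.7 | 0.5 | 15.0% |
| 0.7 | 0.7 | 13.6% |

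The range is thus about 14–19%. The T1 to T2 contrast is left out because it is the difference of the other two changes. Counting it would only add to the figure.

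**3. Power at 64 per arm under each possible win rule, one time point, d = 0.5 on both instruments.** Single-test power is 0.801 at alpha 0.05 and 0.712 at 0.025. Under independence:

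- Both required, each at 0.05: 0.801² = 0.642.
- At least one, under Holm: 1 − (1 − 0.712)² = 0.917.
- Each instrument, under Holm: 0.712 + (0.801 − 0.712) × 0.712 = 0.775.

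Simulated t statistics (126 degrees of freedom, noncentrality 0.5 × √32 = 2.83) extend this to correlated instruments:

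| Win rule | Correlation 0 | Correlation 0.8 |
|---|---|---|
| Both required | 64% | 73% |
| At least one (Holm) | 92% | 80% |
| Each instrument (Holm) | 78% | 76% |

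The normal approximation, which puts single-test power at 80.7%, gives 65–74%, 81–92% and 76–78% for the three rows.

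**The case against.** **It is only a condensed article, and the aim is preliminary.** A separate analysis plan may settle alpha allocation, the role of each analysis set and the handling of subscales, and their absence here is not in itself a fault. The stated aim is feasibility and preliminary efficacy. This stands as far as it goes. However, the article does make two instruments primary, places its correction on paired tests and sizes the trial on an undivided alpha. It also states a superiority hypothesis, and its Discussion links confirmation to public policy.

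**Stronger readings that a reader might infer, and that the article does not support:**

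- *Every outcome test is run at 0.05.* The only alpha stated is in the sample-size paragraph, and a Holm or Bonferroni correction is mentioned. The fair criticism is that this correction is conditional, tied to paired tests and without a family.
- *Ten primary scores at two times, so 20 tests.* That would give 33–55% with the correlations above and 64% under independence. But the four domains and six facets are listed to describe the instruments. Nothing says that each is a primary test.
- *The two analysis sets double the error.* They share most participants. With an assumed correlation of 0.92 between them, the correlated figure moves from 14–17% to 18–22%. The fault is that neither set is primary.
- *Controlling alpha over two instruments necessarily loses the stated power, which falls to 71%.* That is the power of one Bonferroni test at 0.025. If either instrument suffices under Holm, power is about 80–92%.
- *The error rate is shown to exceed 5%.* It does so only if any one success counts, and the article states no win rule.

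**Conclusion.** The point holds in this form: the article fixes no single primary between-arm comparison, and no binding rule governs multiplicity among the between-arm tests. The consequence depends on the missing win rule. If either instrument at T1 or T2 suffices, the family-wise error is about 14–19%, for correlations of 0.3–0.7 between scores and 0.5–0.7 between times, up to independence. If both must succeed at one named time, alpha is not inflated and joint power at 64 per arm is about 64–73% by the t-test (65–74% by the normal approximation), for d = 0.5 and correlation 0–0.8. All power figures rest on d = 0.5, which the article does not state. The error-rate figures do not depend on it.

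**What to change.** Before outcome data are analysed, name one between-arm primary comparison: one defined score of one instrument, one time point, intention-to-treat, one test at two-sided 0.05. Test the other instrument next in fixed order. Make the other time point, the domains and the facets secondary, and the per-protocol analysis supportive. The 64 evaluable and 76 randomised per arm then stand. The sponsor should choose the lead instrument and define its score. The article gives no ground for choosing on its behalf, beyond calling WHOQOL-OLD a complement.

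If both instruments stay primary, apply Holm to the two between-arm tests at the named time point, and state the win rule with its own power. At 64 per arm and d = 0.5 this is about 80–92% for at least one success, 76–78% for each instrument under Holm, or 64–74% if both are required (each then tested at 0.05). The effect size behind these figures should be stated with them.

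The cost is a few sentences, and a less favourable stated power if both instruments must succeed.
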